### Intervention

All participants will receive three interventions at the Outpatient Rehabilitation Service of the University Hospital of Brasília (room F49, blue hall), respecting a 7-days washout interval and the same appointment time, which may be scheduled between 8 and 11 a.m.

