### Statistical analysis and sample size

#### Baseline and outcome data

The baseline characteristics will be shown as the mean ± SD for continuous data (i.e., participant’s age and duration of back pain), and n (%) for categorical data (i.e., gender). To analyze the baseline characteristics, we will perform a One Way analysis of variance, or a Kruskal-Wallis test for continuous data if the data are normally distributed. Shapiro-Wilk test will be used to test data normality. The primary and secondary (EEG and pain) outcomes will be analyzed by 3 × 2 mixed-effects model (group [CV4 - CV 4 sham - Control] x time [pre and post]) to repeated data measures for each continuous outcome variable, we will also assesses if the allocation order will interfere in results, for thus we’ll analyze the order of allocation of CV4 (1^st^, 2^nd^ or 3^rd^) x pre values (CV4 – CV4 sham – Control) at the 3^rd^ exposition, using a one-way Anova or Kruskal-Wallis test. When the analysis of variance indicates significant differences among groups, a post-hoc test (Bonferroni test) will be used to separate the differences between groups before and after the intervention period. Data will be analyzed using Prism 6 software for Mac OS X, and a significance level of *p* ≤ 0,05 will be considered to all variables.

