#### Sample size

The sample size was calculated considering: (1) the two-way analysis of variance (ANOVA); [26] three groups; (3) type I error = 5 % (2-sided); (4) type II error = 20 %; (5) the power of the statistical test = 80 %; and (6) effect size = 20 %. The effect size was obtained considering: (I) the results from the pilot study of Miana et al. [16], which demonstrated a effect of 26 % (pre to post intervention) in the group that received the CV4 technique and (II) Cohen’s *d* which considers 20 % a small effect to calculate sample size and power analysis [27, 28]. Then, it was determined a total of 81 subjects. This calculation was performed in G Power 3 program, version for Mac OS X.

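### The post-hoc tests are both gated by the ANOVA and Bonferroni-corrected, but neither gate nor family is fixed; limited to three contrasts of change, a named gate alone holds 5% and recovers power

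*Protocol article*

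**What the plan says.** The section on baseline and outcome data analyses each EEG and pain outcome with a 3 × 2 model, "group [CV4 - CV 4 sham - Control] x time [pre and post". Pairwise testing is conditional: "When the analysis of variance indicates significant differences among groups, a post-hoc test (Bonferroni test) will be used". The same sentence gives the purpose of the post-hoc test: "to separate the differences between groups before and after the intervention period". The 0.05 level "will be considered to all variables".

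The Intervention section makes this a three-period crossover: "All participants will receive three interventions". The Sample size section plans for an ANOVA with three groups, "type I error = 5 % (2-sided"), "effect size = 20" per cent and "the power of the statistical test = 80" per cent, and arrives at 81 participants. It mentions no allowance for post-hoc correction.

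**The concern.** Two devices guard the same error rate, and two things that decide whether both are needed are left open.

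- **The gate.** A 3 × 2 model offers a condition main effect, a time main effect and their interaction. A significant difference among groups could mean the condition main effect, which averages pre and post values. Only the interaction tests whether the pre-to-post change differs between conditions.
- **The family.** Separating groups before and after the intervention can mean three contrasts of change, six cell contrasts (three pairs at pre, three at post), or three within-condition pre-post contrasts. The pre-intervention comparisons say nothing about treatment.

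At stake is power for the contrast that isolates a CV4-specific effect, CV4 against sham. The sample size is set on an overall test at 5%, but that conclusion would be read from a pairwise test at 0.05/3 = 0.0167 or 0.05/6 = 0.0083. A significant overall test could be followed by no significant CV4-sham contrast.

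**Working it through.** **1. The plan's own figure.** Inputs from the Sample size section: two-way ANOVA, three groups, α = 0.05, power 80%, effect size 20%. Assumption: 20% is Cohen's f = 0.20. For a fixed-effects two-way ANOVA with 6 cells and 2 numerator degrees of freedom, λ = f²N. The smallest N with 80% power is 244 observations, and 244/3 = 81.3. With 81 × 3 = 243 observations, power is 0.798. So 81 reproduces as an overall ANOVA calculation at 5% with no Bonferroni allowance.

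**2. Why the gate suffices for three contrasts of change.** Let the three pairwise nulls be CV4 = sham, CV4 = control and sham = control, all in mean change. If any two hold, all three hold. The only intersection to test is therefore the overall null, and the overall test does that at 5%. If exactly one pair is truly equal, that pair is tested at its own 0.05. This is a complete closed test.

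**3. Error rates, gate alone, that family.** Simulation: 81 completers, normal change scores, sphericity, gate F(2,160), paired t tests with their own error.

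- All three equal: 5.0%.
- Only CV4 differs, by a large amount: 4.9% for the sham-control pair.

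**4. Power, that family.** The effect is not taken from the protocol; it is set so that the gate has 80% power. For F(2,160) at 5% this needs λ = 9.82.

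- CV4 alone differs by d: λ = 81 × (2/3)d², so d = √(9.82 × 1.5/81) = 0.426 residual SD of change.
- Sham has half the CV4 effect: λ = 81 × d²/2, so d = √(9.82 × 2/81) = 0.492.

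Chance of declaring CV4 different from sham (40,000 simulated trials):

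| Pattern | Gate only, 0.05 | Gate + Bonferroni over 3 | Gate + Bonferroni over 6 |
|---|---|---|---|
| CV4 differs, sham = control | 71% | 60% | 51% |
| Sham has half the CV4 effect | 34% | 20% | 14% |

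In the first pattern, among trials with a significant gate (80%), CV4-sham is missed in 1 − 0.714/0.80 = 11%, 1 − 0.604/0.80 ≈ 24% and 1 − 0.509/0.80 = 36% respectively.

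A second set of assumptions (variance shares: subject 0.5, visit 0.2, residual 0.3) gives a similar loss from Bonferroni over three: 0.775 to 0.674 for a CV4 shift of 0.35 total SD, and 0.622 to 0.515 for 0.30 SD. At 0.8 SD, power is 1.00 either way.

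**5. Error rates for the wider families the sentence allows.** Same variance shares, CV4 shift of 0.8 SD, sham and control null:

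| Family | Gate only | Gate + Bonferroni |
|---|---|---|
| Six cell contrasts | 16.1% | 3.0% |
| Three within-condition pre-post contrasts | 9.5% | 3.3% |

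The real CV4 effect opens the gate, and the remaining true nulls are then tested without protection.

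**6. Sensitivity to unequal variances.** With strongly unequal variances and a pooled error term, the three contrasts of change have family-wise error of 9.1% with the gate alone and 3.9% with Bonferroni. With paired tests using their own error, the remaining weakness is the gate itself: 6.6% under the global null, back to 5.0% with a multivariate gate.

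**The case against.** A reader might infer that Bonferroni is redundant as the plan stands and can simply be struck out. The documents do not support that. The argument in step 2 covers three contrasts on one three-level factor, whereas the sentence can describe six cell contrasts or within-condition contrasts, for which step 5 shows that Bonferroni does necessary work. It also needs the interaction as gate and a sound error term, and the text fixes neither.

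A reader might also infer that Bonferroni costs power on every contrast, or convert the loss into extra participants. The first is wrong for large effects, where nothing is lost, and for contrasts that are truly null. The second would compare corrected and uncorrected tests with no gate, which is not the choice here.

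It can fairly be said that an omnibus test followed by Bonferroni is valid, common and conservative: it inflates no error rate and biases no estimate. That stands. So does the point that the power figures rest on a chosen effect. At a within-person correlation of 0.5 and f = 0.20, the 3 × 2 interaction needs only 64 participants in the usual repeated-measures calculation, so 81 may give more than 80% overall power and the loss would then be smaller.

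Finally, an article may leave the gate and the family to a fuller analysis plan. But this sentence does set a rule, and its wording points towards comparisons the trial does not need.

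**Conclusion.** The concern holds as a matter of efficiency and clarity. The plan gates and also corrects, without saying which term is the gate or which contrasts form the family. Restricted to the three differences in pre-to-post change, the gate alone holds 5% per outcome, and Bonferroni over three costs roughly 10 to 14 percentage points of power for CV4-sham at moderate effects (about 20 points over six). On that family, with the same gate and the same tests, the simpler rule rejects everything the corrected rule rejects, and more.

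The power figures assume 81 completers, normality, sphericity and an effect set for 80% overall power. The closed-testing result itself depends on a valid 5% gate and valid pairwise tests, not on the effect size. This is a worthwhile, inexpensive improvement, not an error-rate fault. Under the current wording, Bonferroni should stay.

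**What to change.** Amend the post-hoc sentence in the section on baseline and outcome data, making all four changes together:

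1. Name the condition-by-time interaction (the overall test of condition differences in pre-to-post change) as the gate, with a sphericity correction or as a multivariate test.
2. Limit the post-hoc family to the CV4-sham, CV4-control and sham-control differences in change.
3. Test each at 0.05 with a paired test using its own error term.
4. Only then remove the Bonferroni step.

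The cost is a short text edit, with no extra data or participants. There are three limits. The pairwise confidence intervals will not be simultaneous. The rule is valid only for these three contrasts, so any added comparison needs its own correction. It also controls error per outcome only: the two primary parameters, peak frequency and amplitude, each tested at 0.05, could still give up to 1 − 0.95² = 9.75% if independent, which needs a separate decision.

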One of the most studied OCF techniques is the Compression of the 4th Ventricle (CV4) - the osteopath exerts a compression force on the lateral angles of the squama occipitalis. The CV4 technique affects both central and autonomous nervous system [8], assessed by change in the blood flow and in the tissue oxygen saturation [9, 10]. Another way to measure the effects of the CV4 technique is the brain cortex electrical activity by electroencephalography (EEG), which is a validated method to support the results [11–14]. Current literature has only 2 crossover studies with healthy participants: the work of Cutler et al. [15] showed a decrease in sleep latency; and Miana et al. [16] showed an increase in the absolute power of alpha frequency. The EEG exam is useful to detect changes in the central processing of pain [17] and in patients with chronic pain, one study showed increased power amplitude in alpha frequency bands and a shift towards lower frequencies of the dominant peak [18]. These outcomes are important to develop new trials on diagnosis and therapeutics because of the increasing number of subjects with chronic pain in world [19, 20].

Therefore, this study aims to assess brain cortex electrical activity (alpha band frequency) in individuals with nonspecific chronic low back pain submitted to CV4 technique. The investigators hypothesize that patients with chronic low back pain submitted to the technique would have the peak alpha frequency (PAF) modulated and, thus, would experience physical relaxation.

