### Measurements

#### Primary outcome measurement

The mean change in peak alpha frequency (PAF) will be the primary outcome measure to assess the effects of CV4 technique on nonspecific chronic low back pain. PAF is a measure derived from EEG analysis, and it is defined by two parameters: (1) its occurrence on the frequency axis; and 2) its amplitude on the power density axis. The participants assessment (EEG) and the results statistical analysis will conducted by a blinded researcher ([name]).

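### No comparison is named as deciding the primary hypothesis, so a CV4-control difference without a CV4-sham difference would fit it

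*Protocol article*

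**What the plan says.** All references are to the protocol article.

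- **Hypothesis (Background).** "patients with chronic low back pain submitted to the technique would have the peak alpha frequency (PAF) modulated". No comparator is given; the Abstract and Discussion are worded in the same way.
- **Primary outcome (Primary outcome measurement).** "The mean change in peak alpha frequency (PAF) will be the primary outcome measure to assess the effects of CV4 technique". Again there is no comparator. The section defines the outcome by two parameters, the position of the peak on the frequency axis and its amplitude on the power axis. The Abstract also lists power amplitude and peak frequency as the primary measures.
- **Analysis (Baseline and outcome data).** A 3 × 2 mixed-effects model, condition by time. If the analysis of variance shows differences among groups, "a post-hoc test (Bonferroni test) will be used to separate the differences between groups before and after the intervention period". No comparison ranks above another, and the number of comparisons under Bonferroni is not stated.
- **Sample size.** A two-way ANOVA with three groups, with "type I error = 5 % (2-sided"), "the power of the statistical test = 80" per cent and "effect size = 20" per cent, giving 81 participants. The effect size rests partly on a pilot study that "demonstrated a effect of 26 % (pre to post intervention) in the group that received the CV4 technique", a quantity that involves neither comparator.
- **Conditions (CV4 sham; Control).** Sham places the practitioner's fingers under the occiput for as long as CV4 lasts. Control is lying supine for the same time, without visual or verbal contact.

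**The concern.** The two comparators answer different questions. CV4 against control combines the compression with being touched and attended to. CV4 against sham holds hand contact on the occiput roughly constant and comes closest to testing the technique. The Discussion intends positive results to support use of the technique in a health service, so the claim at stake concerns the technique.

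The plan does not say which comparison settles the matter. Bonferroni limits the chance of any false pairwise rejection, but it does not say which rejection supports the hypothesis. A significant overall test driven by touch, with CV4 different from control and indistinguishable from sham, satisfies a hypothesis that says only that the peak is modulated after CV4. Meanwhile the most informative comparison waits behind an overall gate and shares its alpha with comparisons that bear less directly on the technique.

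**Working it through.** **1. The plan's own figure.** Inputs from Sample size: alpha 0.05, power 80%, three groups, effect size 20%. Read 20% as Cohen's f = 0.20 in a fixed-effects two-way ANOVA with numerator df 2 and 6 cells. The noncentrality is λ = N·f² = 0.04·N.

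- N = 244 observations: power 80.0%.
- 81 people × 3 conditions = 243 observations: power 79.8%.

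So 81 is recovered as an overall three-condition test. A paired contrast with a standardised difference of 0.20 would need 199 people. No single contrast was sized.

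**2. Assumptions for the illustration.** The article gives no SD or correlation for the EEG change. Take pre-to-post change scores with SD 1 in each condition and correlation ρ between conditions from 0 to 0.5, n = 81, no dropout. A mean difference δ between two conditions gives a standardised paired difference dz = δ / √(2(1 − ρ)). The Bonferroni family is taken as the three pairwise comparisons: 0.05 / 3 = 0.0167.

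**3. Touch-only effect.** CV4 and sham are equal, and both differ from control by 0.4 SD.

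- ρ = 0: dz = 0.4 / 1.414 = 0.283
- ρ = 0.5: dz = 0.4 / 1 = 0.40

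Simulated trials follow the stated sequence: an F test of condition on change (equivalent to condition × time) at 0.05, then pairwise tests at 0.0167.

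| Touch effect | CV4-control significant (ρ = 0 to 0.5) | CV4-sham significant |
|---|---|---|
| 0.4 SD | 55% to 88% | about 2% |
| 0.3 SD | 31% to 60% | about 2% |

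At 0.4 SD the problem pattern itself (CV4 beats control and does not beat sham) occurs in about 54% to 87% of trials.

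**4. CV4-specific effect.** CV4 differs from both comparators by the same amount. Power for CV4-sham by the noncentral t, with 80 df and noncentrality dz·√81 = 9·dz. Critical values are 1.990 at 0.05 and 2.445 at 0.0167.

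| dz | 9·dz | At 0.0167 | Single contrast at 0.05 |
|---|---|---|---|
| 0.20 | 1.80 | 27% | 43% |
| 0.315 | 2.835 | 65% | 80% |
| 0.40 | 3.60 | 87% | 94% |
| 0.50 | 4.50 | 98% | 99% |

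Simulating the full sequence with the overall gate at δ = 0.44 SD and ρ = 0 (dz = 0.44 / 1.414 = 0.311) gives about 65% against about 80%. The gate itself therefore costs little; the loss comes from the divided alpha. If Bonferroni covered six comparisons, power at dz 0.315 would be 55%.

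**The case against.** An overall test followed by Bonferroni comparisons is conventional and controls the error rate. CV4-sham would be computed whenever the gate opens, so a CV4-control difference would be reported beside a null CV4-sham result. A ranking of contrasts could also sit in an analysis plan that is not shown. These points are fair. Error control is not the complaint, and the sham result would not be hidden. What remains is that the article states its hypothesis, primary outcome and test sequence, and together they leave open which result counts as success.

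Four stronger readings are tempting and are not supported:

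- **A CV4 pre-to-post change alone could count as success.** The post-hoc step opens only on differences among groups, and the article states no standalone pre-to-post test. A change common to all three conditions would open the gate in only about 5% of trials. The pilot's pre-to-post figure is a source for the effect size, not a success criterion.
- **Bonferroni takes away power promised to CV4-sham.** The sample size was calculated for the overall test at 5%, and that test is run at 5%. Nothing was promised to any contrast.
- **The power loss is large in general.** It is about 15 points near dz 0.3 and 1 point at dz 0.50. At dz 0.20, power is inadequate either way.
- **CV4-sham isolates the compression.** CV4 is given by an osteopath using the thenar eminences, sham by a physiotherapist using the fingers. The contrast carries those differences too.

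**Conclusion.** The point holds as an unnamed deciding comparison. The stated rule lets a CV4-control difference count as support for the hypothesis when CV4 does not differ from sham. The 0.4 SD touch-only case shows that this could be the usual outcome of such a trial and not a rare one. Naming CV4-sham would also raise its power, from about 65% to about 80% near dz 0.31.

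All these sizes depend on the assumed SDs, correlations and effects, on full attendance, and on the inferred family of three. The gap in the decision rule depends on none of them. The trial can still be analysed, but the change should be made before the data are seen, because afterwards the choice of comparison could follow the results.

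**What to change.** In Baseline and outcome data:

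1. Name one primary contrast: CV4 minus sham in pre-to-post change, estimated from the same mixed model and tested two-sided without the overall gate.
2. Test CV4 against control only if that contrast is significant. Treat sham against control and the within-condition pre-to-post changes as descriptive.
3. Settle the two primary parameters. Either name peak frequency or peak amplitude as primary at two-sided 0.05, or divide the alpha between them, for example by Holm. Two independent tests each at 0.05 would give a familywise error of 1 − 0.95² = 9.75%.
4. State that the hypothesis is supported only if CV4 differs from sham, and note that this contrast still carries the difference in practitioner and hand contact.

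The cost is wording only, with no new data or participants. A CV4-control difference alone could no longer be claimed as a positive result. If the alpha is divided, the first Holm step is at 0.025, where power at dz 0.315 is about 71%: less than the 80% of a single test, but still above 65%.

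### The Bonferroni follow-up tests read as comparing conditions at pre and again at post, although the outcomes are changes; three between-condition contrasts of change should be named instead

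*Protocol article*

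**What the plan says.** Under Primary outcome measurement: "The mean change in peak alpha frequency (PAF) will be the primary outcome measure". The Secondary outcome measurement section likewise defines the pain outcome as a mean change, measured before and immediately after each session.

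Under Baseline and outcome data, both outcomes are analysed by a "3 × 2 mixed-effects model (group [CV4 - CV 4 sham - Control] x time [pre and post" layout with repeated measures. The follow-up step is conditional: "When the analysis of variance indicates significant differences among groups", then "a post-hoc test (Bonferroni test) will be used to separate the differences between groups before and after the intervention period". The section does not list the comparisons or say how many share the Bonferroni correction. It also plans a check of whether the position of CV4 in the order affects the pre values at the third exposure.

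**The concern.** In a condition-by-time layout, the question raised by a change outcome is whether the pre-to-post change differs between conditions. The group-by-time term answers this for the three conditions jointly. Only the follow-up tests say whether CV4 differs from sham, the comparison that separates CV4 from touch and rest.

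The sentence describing those tests speaks of group differences before and after the intervention. Its most literal meaning is three pairwise comparisons at pre and three at post. That has two consequences.

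- A difference between conditions before anything has been done reflects chance or carry-over, not treatment. Tests at that point use up part of the error rate without informing the conclusion.
- A comparison of post values alone takes no account of where each condition started. If pre values differ by condition, it can show an effect where changes are equal, or hide one where they differ.

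**Working it through.** **Inputs.** From Sample size: "type I error = 5 % (2-sided"), "the power of the statistical test = 80" %, "effect size = 20" %, based on "the two-way analysis of variance (ANOVA"), and 81 participants. From Intervention: every participant receives all three conditions. The protocol gives no standard deviation or correlation, so those below are assumptions.

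**The plan's own figure.** With f = 0.20, numerator df 2 and six cells, a fixed-effects two-way ANOVA needs 244 observations for 80% power, and 244/3 = 81.3. With 81 × 3 = 243 observations the power is 0.798. So 81 reproduces if the 20% is read as f and the observations as independent. The figure concerns the overall test and says nothing about the follow-up contrasts; it is used here only as n.

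**Step 1: cost of the pre-intervention tests.** A contrast with 80% power at two-sided 0.05 has noncentrality 1.96 + 0.84 = 2.80. With k tests, power is Φ(2.80 − z), where z is the two-sided critical value at 0.05/k.

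| Tests in family | Critical value | Power |
|---|---|---|
| 1 | 1.960 | 0.80 |
| 3 | 2.394 | 0.66 |
| 6 | 2.638 | 0.56 |

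Going from three tests to six costs about 9 percentage points. The paired t version with n = 81 agrees: at a standardized paired difference dz = 0.30 (assumed), power is 0.60 with three tests and 0.50 with six. The dz needed for 80% power rises from 0.367 to 0.396.

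**Step 2: post contrast against change contrast.** Simulation of the crossover with n = 81, alpha 0.05/3 = 0.0167, and assumed SDs of 0.7 (person), 0.5 (session) and 0.5 (error). Any pre shift is assumed to persist in full to the post recording of the same session. Entries are rejection rates for CV4 against sham.

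| Pre difference | Effect on change | Post contrast | Change contrast |
|---|---|---|---|
| 0 | 0 | 1.7% | 1.8% |
| 0 | 0.3 | 61% | 61% |
| 0.25 | 0 | 43% | 1.7% |
| −0.3 | 0.3 | 1.8% | 61% |

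The two tests agree when expected pre values are equal and diverge when they are not.

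The last two rows are stress cases. If all orders are equally likely, CV4 precedes sham in half of them, so a CV4 effect of 0.3 that persisted undiminished would shift the mean pre difference by 0.5 × 0.3 = 0.15. The post difference would then be 0.3 − 0.15 = 0.15. Under these SDs the paired difference has variance 2 × (0.25 + 0.25) = 1, so dz is about 0.15. The paired t calculation then gives power of about 0.14 at alpha 0.0167, against 0.60 for the change contrast.

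**Step 3: change or baseline adjustment.** Let ρ be the correlation between the pre and post between-condition differences. Relative to the post contrast, the change contrast has variance 2(1 − ρ) and the baseline-adjusted contrast 1 − ρ².

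| ρ (assumed) | Change | Baseline-adjusted |
|---|---|---|
| 0.5 | 1.00 | 0.75 |
| 0.75 | 0.50 | 0.44 |

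Inverting the last column, unadjusted post values have 1/0.75 = 1.33 and 1/0.4375 = 2.29 times the variance of baseline-adjusted ones. This supports the baseline-adjusted option only: at ρ = 0.5 change scores gain no precision over post values. The SDs in step 2 imply ρ = 0.5, which is why both contrasts reject 61% in the second row.

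**The case against.** A reader might infer that no follow-up test addresses the primary outcome. The document does not support that. The group-by-time term tests change. With randomized order and no carry-over, expected pre values are equal, so a post contrast estimates the same effect as a contrast of changes, as the second row of step 2 shows. Chance imbalance alone does not inflate the error rate either (first row). It misleads only in the sense that, in a trial where pre values happen to differ, the post contrast inherits part of that difference.

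A reader might also take the sentence to mean pre against post within each condition and fear a conclusion of the form that CV4 changed and sham did not. If all conditions shift equally, changes are independent and each such test has 50% power, that pattern arises in 0.5 × 0.5 = 25% of trials. But the sentence speaks of differences between groups, and the tests open only after a significant overall result. With that gate, under the SDs of step 2, the pattern occurs in about 1% to 2% of trials. The 25% is no measure of risk for this plan.

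The sentence can, thirdly, mean that before-to-after differences are compared between groups. The change outcomes and the group-by-time layout favour this, and the article's English is loose. This objection stands in part: the wording is ambiguous, and the family of six is inferred, not stated.

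Finally, listing contrasts is commonly left to a full protocol or analysis plan, which is not shown. The point here is narrower. The article does state what its follow-up tests compare, and states it in a form that does not match its outcomes.

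**Conclusion.** The point holds in a limited form. As literally written, the follow-up tests include pre-intervention comparisons that carry no information about CV4, and post comparisons that are sound only if pre values are balanced across conditions. The protocol does not take that balance for granted, since it plans an order check on pre values.

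The cost of the first weakness is about 9 points of power (66% to 56%), and only if the Bonferroni family is six rather than three. The second has no fixed size: it is nil with balanced pre values and can be large otherwise. The illustrations rest on assumed SDs and on a pre shift that persists to the post recording.

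The overall test of change is unaffected. This is a correction worth making before analysis, not a fault that invalidates the plan.

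**What to change.** Replace the post-hoc sentence under Baseline and outcome data with one stating that:

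- the follow-up tests are the pairwise condition-by-time contrasts, that is, between-condition differences in change or in baseline-adjusted post values, with one of the two chosen in advance;
- the contrasts are CV4 against sham, CV4 against control, and sham against control;
- Bonferroni applies to these three only, within each outcome variable;
- conditions are not tested against each other before the intervention as part of this family.

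The separate order check on pre values can stay. The change costs one sentence, with no additional data, visits or participants.
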